
## **10. Analysis Plan**

Prior to analysis, we will produce data summaries including graphical methods to assess data quality, examine central tendencies and distributional assumptions and randomization success. The primary analysis will consist of unadjusted intent-to-treat hypothesis tests using the logrank test to compare the time to hospitalization in the two groups. We will also estimate Cox proportional hazards regression models adjusted for the stratification variable and other covariates of interest (such as patient sex, income, race, baseline ejection fraction, and quality of life), retaining these given evidence of confounding or predictive ability. We will employ a confounder selection method based on "change in estimate" criterion. We will assess interaction terms between the a priori potential effect modifiers such as income level, race, and baseline ejection fraction. All hypothesis tests will be two-sided and models will be assessed using standard diagnostic techniques.(66-68) We will use standard approaches to assess the proportional hazards assumption and include interaction terms with time if necessary. We will also fit frailty models to analyze repeated rehospitalizations within patients; these models properly adjust for the correlation of multiple events within individuals. Handling of missing data is an important issue in all RCTs. Follow-up data may be missing if participants miss the follow-up visit or withdraw. Even in subjects who are lost to follow-up, however, we will be able to capture any events that result in hospitalization, and thus will still be able to observe our primary outcome. We will compare dropout

rates by arm, will attempt to find the reasons for missing data and will compare baseline characteristics in participants with complete vs. incomplete follow-up. In secondary analyses we will investigate the sensitivity to modeling assumptions using imputation models and inverse probability-weighted estimating equations and models that adjust for informative missing data.

## **11. Subject Confidentiality**

To ensure that patient, physician, and other informant confidentiality is preserved, individual identifiers (such as name and medical record number) are stored in a single password protected system that is accessible to study research, analysis and IT staff only. This system is hosted on site at UPenn and is protected by a secure firewall. Once a participant is in this system, they will be given a unique study identification number (ID). Any datasets and computer files that leave the firewall will be stripped of all identifiers and individuals will be referred to by their study ID. The study ID will also be used on all analytical files. Please see attached document (WTH database security grant-protocol text FINAL) for full database security details. The medication adherence device will provide adherence data from each participant. This information is transmitted via cellular signal without any subject identifiers.

### **11.1. Subject Privacy**

Privacy refers to the person's desire to control access of others to themselves. Privacy concerns people, whereas confidentiality concerns data. Describe the strategies to protect privacy giving consideration to the following: The degree to which privacy can be expected in the proposed research and the safeguards that will be put into place to respect those boundaries. The methods used to identify and contact potential participants. The settings in which an individual will be interacting with an investigator. The privacy guidelines developed by relevant professions, professional associations and scholarly disciplines (e.g., psychiatry, genetic counseling, oral history, anthropology, psychology). At the time that UPenn study staff receives patient data, they will upload the patient data into the secure, web-based database (REDCap) and a study ID number will be generated for each patient. A link between the study ID number and the patient PHI will need to be maintained to ensure that the study staff can track recruitment efforts to potential participants and to avoid contacting any patients who have previously declined to participate. To ensure that patient confidentiality is preserved, individual identifiers (such as name) are stored in a single password protected system that is accessible to study research, analysis and IT staff only. This system is hosted on site at UPenn and is protected by a secure firewall. Once a participant is in this system, they will be given a unique study ID number. Any datasets and computer files that leave the firewall will be stripped of all identifiers besides the study ID and individuals will be referred to by their study ID only. The study ID will also be used on all analytical files. REDCap is a secure web application for building and managing online surveys and databases. The institution installing REDCap will store all data captured in REDCap on its own servers. Therefore, all project data is stored and hosted at the local institution (UPenn) and no project data is ever transmitted at any time by REDCap from this institution to another institution or organization. Privacy of all study data will be maintained by restricting access to the identifiable information only to approved study staff who have received subject confidentiality and privacy training. Study coordinators will access patient contact information from the database to conduct recruitment phone calls. The study coordinator will review the consent script, which will include a description of the voluntary nature of participation, the study procedures, risks and potential benefits in detail. Participants will be told that all information will be kept strictly confidential, except as required by law. Subjects will be provided a copy of the consent document. All efforts will be made by study staff to ensure subject privacy. Enrollment will be conducted by the study coordinators who will enter patient information directly into the WTH platform once a participant has consented to participate. This

Remote monitoring and behavioral economics in managing patients discharged from the hospital with heart failure: a randomized clinical trial

database is hosted on a secure server as detailed in the subject confidentiality section. Study coordinators may have to contact patients in the intervention and their support partners during the course of the study and will use the WTH database to access contact information to facilitate this contact. If the rate of non-adherence to medication and to weighing-in, as recorded by the medication adherence device and scale, rises above a certain threshold, the study team may also contact the participant's managing physician. If a participant's weight rises above a certain threshold across a specific time period, the study team may contact the participants managing physician to notify them. This will be explained to the participant in the consent process and when the details of study participation are explained by the coordinator. PHI will not be shared with anyone outside the parameters of the study as detailed in the Consent/HIPAA process.

#### *11.2. Data Disclosure*

The following entities, aside from members of the research team, may receive PHI for this research study: CleverCap; The Office of Human Research Protections and the University of Pennsylvania; federal and state agencies (for example, the National Institutes of Health); and, other domestic or foreign government bodies if required by law and/or necessary for oversight purposes

#### *11.3. Data confidentiality*

The following methods will be employed to protect patient PHI for this research study:

x Paper-based records will be kept in a secure location and only be accessible to personnel involved in the study.

x Computer-based files will only be made available to personnel involved in the study through the use of access privileges and passwords.

x Prior to access to any study-related information, personnel will be required to sign statements agreeing to protect the security and confidentiality of identifiable information.

x Wherever feasible, identifiers will be removed from study-related information. A Certificate of Confidentiality will be obtained, because the research could place the subject at risk of criminal or civil liability or cause damage to the subject's financial standing, employability, or liability.

x A waiver of documentation of consent is being requested, because the only link between the subject and the study would be the consent document and the primary risk is a breach of confidentiality. (This is not an option for FDA-regulated research.)

x Precautions are in place to ensure the data is secure by using passwords and encryption, because the research involves web-based surveys.

### **12. Consent Process Overview**

We are requesting a waiver of the requirement to document consent and HIPAA authorization with a signature for participants enrolled into this study since we believe that the research presents no more than minimal risk of harm to subjects and involves no procedures for which written consent is normally

required outside of the research context. [45 CFR 46.117(c)(2)] Some participants will enroll in this study via a remote recruitment process, and therefore, we will read the IRB-approved Consent/HIPAA script over the phone to each participant and ask them to provide verbal consent and verbal HIPAA authorization for use of their data in the study. After a patient provides verbal consent, the coordinator will select this option on the Consent/HIPAA screen on the participants profile that was created during enrollment on the WTH platform for this study. A copy of the Consent/HIPAA document will be included in the device packet provided to them in the hospital (if enrollment occurred in the hospital) or sent to the patients home address (if enrollment was conducted remotely). Participants recruited in the hospital prior to their discharge will be asked to provide their signature for HIPAA authorization. They will also be provided a copy of the Consent/HIPAA document.

#### 12.1. *Potential Study Risks*

As this study does not involve any medical decision making and only observes the use of social behavioral approaches to encouraging patients to use evidence-based treatments that their providers have prescribed them following their CHF diagnosis, we consider this study to be minimal risk. The primary risk would be from a breach of confidentiality involving electronic medical record reviews and monitoring of medication adherence with a medication adherence device and monitoring of weights from an electronic scale, which will be maintained on the WTH platform. This risk has been mitigated by extensive privacy protection protocols, a highly secure data storage system, and a plan to remove identifiers from the data wherever possible. In addition, all study personnel will be held to high standards of upholding confidentiality and safeguarding patient privacy

#### 12.2. *Potential Study Benefits*

This study is to test a new approach to chronic disease management that combines remote monitoring devices and behavioral economic engagement incentives to reduce rehospitalization rates among patients with CHF. The immediate benefits of this study for participants may include improvement for management of CHF, which may lower their risk for future morbidity and death, improved quality of life, and reduced medical care costs. Patients will be randomized into either an intervention group that receives the medication adherence device and scale or a control group that receives usual care. The potential public health impact of a successful intervention to improve management of CHF is enormous and could reduce the number of deaths in the United States substantially each year. The benefits of this research to the participants studied, and to society at large, far surpass the minimal risks.

#### 12.3. *Alternatives to Participation*

Patients are free to decline participation in this study. If they decline to participate, they will receive no reduction in the usual care received from their health care providers for this condition.

#### 12.4. *Data and Safety Monitoring*

While we consider this study to present minimal risk to participants, we have established a Data Safety Monitoring Board of experts in statistics and congestive heart failure to monitor adverse events that may occur among our study participants. The DSMB will be convened every six months (or more often if needed) and will review reports of discharge data for adverse events and assess for safety. Adverse events may also be self-reported by participants. This information will be reviewed by a physician on our study team and will be reported to the IRB in according to all reporting regulations. The following

Remote monitoring and behavioral economics in managing patients discharged from the hospital with heart failure: a randomized clinical trial

517 documents are currently attached to this item: There are no documents attached for this item. Risk /  
518 Benefit Assessment Current limitations to managing CHF are a major public health problem with few  
519 scalable, cost-effective solutions. This study will test a novel behavioral economic intervention. We  
520 believe that this approach will provide the research and public health communities with important  
521 information that can lead to broad generalizability in treating people with CHF at risk for hospitalization  
522 and death nationally. With the large scientific and public health benefits of the knowledge gained from  
523 this study, the minimal risks to participants are reasonable in relation to the importance of the  
524 knowledge that reasonably may be expected to result.

525

526 Final Study Protocol

527 **Table of Contents**

|     |                                                             |           |
|-----|-------------------------------------------------------------|-----------|
| 528 | 1. Abstract .....                                    | 20 |
| 529 | 2. Background .....                                  | 20 |
| 530 | 3. Overall Objectives .....                          | 21 |
| 531 | 4. Aims .....                                        | 21 |
| 532 | 4.1. Primary Aims .....                              | 21 |
| 533 | 4.2. Secondary Aims .....                            | 22 |
| 534 | 5. Primary Outcome Variable.....                     | 22 |
| 535 | 6. Secondary Outcome Variable(s) .....               | 22 |

## 1. Abstract

Using a 2-arm, randomized, controlled trial (RCT) among CHF patients at the University of Pennsylvania Health System (UPHS), we propose to test the effectiveness of applying automated hovering to improve outcomes among CHF patients at high risk of readmission. To conduct this trial we will leverage the Penn Data Store, an electronic repository that can be used to identify study cohorts, and the NIH-funded Way to Health platform, which provides linkages between home-based remote monitoring devices and a server that can provide automated feedback to patients. The primary outcome will be hospital readmission rate during the 12 months of study enrollment. Secondary outcomes will include the total cost of hospitalizations. We will enroll patients who have been discharged from UPHS with CHF at least once in the past 12 months and randomize them to either: [1] usual care with no additional intervention; [2] the provision of wireless pill bottles and scales with daily lottery incentives to encourage daily adherence [3] the designation of a friend or family member to be a support partner for patient [4] alerts to the patient's clinician through the EMR for verified weight gains. The overall objective is to leverage access to the UPHS CHF clinic, EPIC resources for identifying eligible patients, and the Way to Health platform to launch and enroll a practical clinical trial powered to detect differences in hospital readmission rates using remote monitoring devices for automated hovering for CHF management. Primary outcome variable(s) include re-hospitalization rate over 12 months of enrollment. Secondary outcome variable(s) include: 1) To assess the cost-effectiveness of the intervention relative to usual care 2) assess cause-specific rehospitalizations.

## 2. Background

About 5.8 million Americans have CHF; 1 in 6 will develop CHF during their lifetime; and CHF is one of the most common reasons for hospital admission, hospital readmission, and a major cause of morbidity, mortality, and increasing health care costs. Among all adult patient groups, older patients with CHF have the highest rate of rehospitalization (27% within 30 days of discharge), with annual health care costs exceeding \$24.3 billion. This is because patients discharged after a CHF hospital admission face many challenges, including a complex array of medications and follow-up care and the need for daily self-management, including significant lifestyle changes. Current approaches to the management of CHF show mixed elements of promise and disappointment. Complex disease management, some involving remote monitoring and some with intensive and expensive case management by nurse practitioners, have been shown in some small studies to reduce readmissions and improve survival and quality of life, but they are costly and require a workforce that is unlikely to be economically feasible to support. In addition, more recent and larger studies suggest that these approaches are ineffective. At the other extreme, trials of self-management using patients as their own workforce through intensive training demonstrate no mortality or rehospitalization benefit. These results suggest that neither conventional telemonitoring assessing symptoms and weight, nor self-management, is likely to offer promise in CHF management. A significant challenge to the effectiveness of remote monitoring programs in practice is that many patients offered such support do not participate at all and many who do participate lose interest rapidly. In our own clinics, we have found that simply providing remote monitoring devices to patients at high risk of disease exacerbations is not enough, as utilization rates of remote monitoring devices in a group asked to do this daily declined steadily over time without engagement incentives such that by 3 months patients did remote monitoring of blood pressure and blood sugars on only 50% of days. This implies that to be successful in changing behavior of patients whose behavior has likely contributed to their being high risk, remote monitoring and engagement enhancements need to be combined. There is consensus that the effective management of CHF depends on medication adherence, dietary management (particularly sodium), and weight management (to monitor fluid balance). Medication adherence and weight are much easier to monitor than food intake. Low adherence to CHF

medications is associated with more admissions and higher mortality. Non-adherence rates are high, with estimates ranging from adherence to angiotensin-converting enzyme inhibitors of only 60% at 1 year to full adherence, defined as filling enough prescriptions to have medication available each day for 1 year, as low as 10%. The data on the importance of weight management for CHF patients is compelling; often the earliest sign of pending decompensation is a gain in weight of several pounds that presages clinical deterioration, which can be avoided by early intervention. Weight monitoring adherence (odds ratio [OR] 0.42, 95% confidence interval [CI] 0.23-0.76) and diuretic self-adjustment adherence (OR 0.44, 95% CI 0.19-0.98) have been found to be associated with lower adjusted odds of CHF-related ED visits or hospitalizations. For these reasons, we will focus on adherence to both daily weights and diuretic use in this intervention. Further, this study would be the first to experimentally test the impact on CHF management of remote medication adherence and weight monitoring along with behavioral economic engagement incentives. The engagement incentives will help us attain much higher rates of ongoing participation by high-risk patients than otherwise would be likely. This approach will enable extension of clinical services outside the clinician offices utilizing an existing technology-based approach with built in automatic feedback loops (including small, but frequent incentives that have been extensively tested in other contexts) to ensure high rates of adherence, which is an approach that minimizes personnel costs relative to traditional disease management.

### **3. Overall Objectives**

To leverage access to the UPHS CHF clinic, EPIC resources for identifying eligible patients, and the Way to Health platform to launch and enroll a practical clinical trial powered to detect differences in hospital readmission rates using remote monitoring devices for automated hovering for CHF management.

### **4. Aims**

#### *4.1. Primary Aims*

Re-hospitalization rate over 12 months of enrollment

#### *4.2. Secondary Aims*

1. To assess the cost-effectiveness of the intervention relative to usual care 2. assess cause-specific rehospitalizations

### **5. Primary Outcome Variable**

The primary comparison will be the times to events compared between the intervention arm and the usual care arm; that is, the primary hypothesis is whether a series of interventions, adapted to the behavior and outcomes of each particular patient, will reduce readmission rates compared to usual care.

### **6. Secondary Outcome Variable(s)**

In secondary analyses the comparison will also be times to events compared between the intervention and the usual care arm for cause-specific rehospitalizations. Cost-effectiveness ratios will be calculated as the difference in costs divided by the difference in rehospitalization rate calculated under Specific Aim 3 for the “within-trial” analysis.

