## Remote monitoring and behavioral economics in managing patients discharged from the hospital with heart failure: a randomized clinical trial

usual care arm based on data obtained on our target population at UPHS. We wish to have 80% power to detect an absolute decrease in this rate of about 10% in the intervention group; this corresponds to a hazard ratio of 0.73. We will accrue 566 patients over the 24-month enrollment period and follow them for an additional 12 months; with the 1:1 randomization ratio, we will have approximately 283 subjects in each arm. The primary hypothesis test will use a two-sided Type I error rate of 0.05. Note that the power calculations are based on the time to first readmission; if patients experience multiple readmissions, statistical power will be increased. Prior to analysis, we will produce data summaries including graphical methods to assess data quality, examine central tendencies and distributional assumptions and randomization success. The primary analysis will consist of an unadjusted intent-to-treat hypothesis tests using the Andersen-Gill formulation of the Cox proportional hazards model to compare the times to hospitalizations in the two groups; these models properly adjust for the correlation of multiple repeated events within individuals. We will also estimate multivariate regression models adjusted for the stratification variable and other covariates of interest (such as patient sex, income, race, baseline ejection fraction, and quality of life), retaining these given evidence of confounding or predictive ability. We will employ a confounder selection method based on "change in estimate" criterion. We will assess interaction terms between the a priori potential effect modifiers such as income level, race, and baseline ejection fraction. All hypothesis tests will be two-sided and models will be assessed using standard diagnostic techniques. We will use standard approaches to assess the modeling assumptions and include interaction terms with time if necessary. Handling of missing data is an important issue in all RCTs. Follow-up data may be missing if participants miss the follow-up visit or withdraw. Even in subjects who are lost to follow-up, we will be able to capture any events that result in hospitalization, and thus will still be able to observe our primary outcome. This includes hospital discharges from Penn Medicine as well as obtaining state-based discharge data and from Pennsylvania, New Jersey and Delaware to ensure that all readmissions that occur outside of Penn Medicine are captured. In addition, some subjects may receive a heart transplant during the course of the study. Because the disease trajectory and treatment paradigm change significantly with that event, we will censor patients at the time of transplant; the admission to conduct the transplant will count as an event, but follow-up will cease then and patients will be removed from the risk set. We will compare dropout rates by arm, will attempt to find the reasons for missing data and will compare baseline characteristics in participants with complete vs. incomplete follow-up. If enrolled intervention patients receive a heart transplant or ventricular assist device during their 12 month participation they will no longer be eligible to participate in the remote monitoring and their data will be censored from the date they receive the transplant or VAD going forward. An additional secondary endpoint will be cause-specific rehospitalizations, the rationale being that evaluating cause-specific hospital admission will allow a more complete understanding of the potential effects of the intervention, by indicating how many of the readmissions are due to what cause (e.g., heart failure, MI, stroke, other cardiovascular cause, noncardiovascular cause, etc). In secondary analyses we will investigate the sensitivity to modeling assumptions using imputation models and inverse-probability-weighted estimating equations and models that adjust for informative missing data. Patient days spent hospitalized, in rehab or at a SNF will not count towards adherence and will be removed from numerator and denominator and considered unmeasurable for adherence. For the qualitative interviews, the Research Scientist and Clinical Research Coordinators will review all data for recurring themes. As our interest is in the differences and similarities between the groups of patients noted above, we will conduct cross-case analyses to identify the factors that may be associated with patient adherence and readmission. The analysis will consist of describing factors in each of the groups and then comparing those factors across groups.

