
To assess the cost-effectiveness of the interventions, we will use analytic methods for economic evaluations in clinical trials. Our approach will be similar to Specific Aim 3 using cost as the outcome. We

Remote monitoring and behavioral economics in managing patients discharged from the hospital with heart failure: a randomized clinical trial

will use generalized linear models to adjust for the stratification variable and other factors. Cost-effectiveness ratios will be calculated as the difference in costs divided by the difference in rehospitalization rate calculated under Specific Aim 3 for the “within-trial” analysis, with parametric 95% CIs for the cost per percentage point increase in adherence and acceptability curves. Standard errors and the correlation of the difference in cost and effect will be obtained using a bootstrap procedure. A further cost-effectiveness analysis from the “societal perspective” will be conducted to assess the impact of the rehospitalization rate reductions measured as cost per QALY gained. To address uncertainty in the micro simulation model, we will also conduct a probabilistic sensitivity analysis (PSA162) by defining probability distributions for the variables in the model used to calculate costs and effectiveness. We will use the results of the PSA to calculate confidence (or credible) intervals and acceptability curves

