## Final Statistical Analysis Plan

### Statistical considerations

Power and sample size issues. Our primary outcome is time to readmission for any cause. The primary comparison will be the times to events compared between the intervention arm and the usual care arm; that is, the primary hypothesis is whether a series of interventions, adapted to the behavior and outcomes of each particular patient, will reduce readmission rates compared to usual care.

We expect the 1-year event rate to be 47% in the usual care arm based on data obtained on our target population at UPHS. We wish to have 80% power to detect an absolute decrease in this rate of about 10% in the intervention group; this corresponds to a hazard ratio of 0.73. We will accrue 566 patients over the 24-month enrollment period and follow them for an additional 12 months; with the 1:1 randomization ratio, we will have approximately 283 subjects in each arm. The primary hypothesis test will use a two-sided Type I error rate of 0.05. Note that the power calculations are based on the time to first readmission; if patients experience multiple readmissions, statistical power will be increased.

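### The cost-effectiveness ratio cannot by itself tell a good result from a bad one, and its interval is uninformative whenever the readmission difference is not significant

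*Supplement*

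**What the plan says.** Cost-effectiveness is the first secondary aim in section 4.2 of the final protocol. Section 6 defines the within-trial result: "Cost-effectiveness ratios will be calculated as the difference in costs divided by the difference in rehospitalization rate". Section 10 of the final protocol and the cost-effectiveness part of the final SAP repeat this definition and add three things:

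- parametric 95% confidence intervals, worded as the cost for each percentage-point gain in adherence and not per readmission;
- acceptability curves, named in the same sentence;
- resampling for the inputs: "Standard errors and the correlation of the difference in cost and effect will be obtained using a bootstrap procedure".

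A societal cost-per-QALY analysis and a probabilistic sensitivity analysis, with its own acceptability curves, follow.

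The final texts do not say in which direction the denominator is taken, which parametric method gives the interval, or what is reported when the ratio is negative or the denominator is near zero. They also leave open whether the rehospitalization rate is the proportion of patients readmitted or the number of admissions per patient. They refer to a Specific Aim 3 for its calculation, but section 4 lists no such aim.

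**The concern.** The intervention is meant to lower readmissions, and readmissions cost money. A result with lower cost and fewer readmissions is therefore one of the hoped-for outcomes. In that case numerator and denominator are both negative and the ratio is positive. It is also positive when the intervention costs more and readmissions rise. A reader given only the ratio cannot tell the two apart.

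The second difficulty is the interval. A ratio behaves badly when its denominator may be close to zero. Fieller's method then gives an unbounded set. A delta-method interval stays finite but hides the instability. Rewording the interval from adherence to readmissions would correct the units and leave both difficulties in place.

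At stake is whether a listed secondary outcome can be interpreted if the trial finds a saving, a small effect or no effect. The primary inference is not touched.

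**Working it through.** **Inputs (final SAP, Statistical considerations; same text in final protocol section 10).** The control rate: "We expect the 1-year event rate to be 47% in the usual care arm". The planned effect: "We wish to have 80% power to detect an absolute decrease in this rate of about 10% in the intervention group", so 47% against 37%. The plan equates this to a hazard ratio of 0.73. It expects about 283 patients per arm and tests at two-sided 5%. Section 7.3 of the final protocol gives each participant 12 months of follow-up.

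**The plan's own figures.** No precision is stated for the ratio, so the nearest figures are the hazard ratio and the power.

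- Hazard ratio: ln(0.63)/ln(0.53) = 0.728, which reproduces 0.73.
- Power with 12 months per participant: expected events = 566 × (0.47 + 0.37)/2 = 238. Then √238/2 × |ln 0.73| = 2.43, and Φ(2.43 − 1.96) gives about 68%.
- Power with follow-up to a common study end (1 to 3 years, exponential hazards): the mean event probability is 0.645. Power is 80.6% with 500 patients and 85.2% with 566 before any allowance for censoring.

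The stated 80% is therefore not reached on 12-month data. That is a separate matter, but it explains why two figures appear below.

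**Sign (illustrative amounts).**

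- Saves $1,000, 10 points fewer readmitted: −1,000/−0.10 = $10,000.
- Costs $1,000 more, 10 points more readmitted: +1,000/+0.10 = $10,000.
- With the denominator reversed to readmissions avoided, both become −$10,000. Reversing it does not remove the ambiguity.

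**Interval.** A Fieller 95% set is bounded only if the estimated denominator d satisfies d² > 1.96² × Var(d), that is, if the readmission difference is significant at two-sided 5%. The cost variance and the cost-effect correlation do not enter this condition. With *rate* read as the 12-month proportion:

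- SE = √(0.47 × 0.53/283 + 0.37 × 0.63/283) = 0.0413
- expected z = 0.10/0.0413 = 2.42
- P(unbounded) = Φ(1.96 − 2.42) − Φ(−1.96 − 2.42) = 0.32

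| True situation | Expected z | P(unbounded) |
|---|---|---|
| 47% vs 37%, 283 per arm | 2.42 | 32% |
| Comparison truly has 80% power | 2.80 | 20% |
| 47% vs 42% (SE 0.0417) | 1.20 | 78% |
| No effect | 0 | 95% |

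Taking the intervention rate from the hazard ratio of 0.73 (37.1%) gives 33% in the first row.

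**If *rate* means admissions per patient-year.** The documents give neither a mean nor a dispersion, so these are assumptions. For negative binomial counts with dispersion θ, the mean that leaves 53% event-free is (0.53^(−θ) − 1)/θ, and the variance is μ + θμ².

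- Poisson: about 21%.
- θ from 0.5 to 2, both arms matched to 47% and 37% with any admission: 16% down to 7%. At θ = 1 the means are 0.887 and 0.587, z = 3.12, giving 12%.
- θ from 0.5 to 2, rate ratio 0.73: 27% up to 42%. At θ = 1 the means are 0.887 and 0.647, z = 2.43, giving 32%.

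**Net benefit on the same sign example.** Net benefit is the threshold times readmissions avoided, minus extra cost. At an illustrative threshold of $10,000 the first case gives 10,000 × 0.10 + 1,000 = +$2,000. The second gives 10,000 × (−0.10) − 1,000 = −$2,000. The two cases separate. The standard error is √(λ²·SE_E² + SE_C² − 2λ·ρ·SE_E·SE_C), with λ the threshold, SE_E and SE_C the standard errors of the effect and cost differences, and ρ their correlation. It is finite whatever the effect.

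**The case against.** The strongest reply is that the plan already holds most of the remedy. An acceptability curve gives the probability that net benefit is positive at each threshold. It stays defined when the denominator is near zero, and it separates the dominant from the dominated case. Bootstrap standard errors and the correlation are planned too. The documents do not rank these summaries, so calling the ratio the headline would be the reader's choice. The sign ambiguity also matters only if the ratio is printed without its two differences.

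This stands, and it rules out a stronger reading that a reader might infer: that the plan has no sound cost-effectiveness analysis. What remains is that the ratio and a parametric interval are still committed to, section 6 names only the ratio, and no rule says when the ratio may be quoted.

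It is also fair that the documents name neither Fieller nor the delta method, and that the interval as written is in adherence units. The percentages above therefore describe what a Fieller interval for the quoted ratio would do, not an interval the plan specifies. They are one minus the power of the readmission comparison; any trial-based ratio inherits that weakness.

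A further tempting inference is that sign confusion would be frequent in this trial. The documents cannot support a frequency. Section 8.5 gives the incentive payments, but no device, staff or per-admission cost is stated.

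**Conclusion.** The point holds as a gap in the reporting of a secondary outcome. The sign ambiguity is certain and needs no assumption. The interval problem has a size only under a stated reading: with the 12-month proportion, 47% against 37% and 283 per arm, a Fieller 95% interval would be unbounded in about 32% of trials, 20% if the comparison truly had 80% power, and about 95% with no effect.

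A reader might take one third as a general property of the plan. The documents do not support that. For recurrent admissions, which the final primary analysis counts, the assumed scenarios run from 7% to 42%, and the plan does not say which denominator applies.

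The change is worth making because it is cheap and uses quantities already planned.

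**What to change.** In sections 6 and 10 of the final protocol and in the cost-effectiveness part of the SAP:

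1. Define the effect as readmissions avoided, usual care minus intervention, and say whether this is a 12-month proportion or admissions per patient.
2. Report the cost difference and the effect difference separately, each with a 95% confidence interval.
3. Replace the parametric interval for the ratio, including its adherence wording, by incremental net benefit with a 95% interval across the thresholds of the planned acceptability curve.
4. Quote the ratio only when the intervention costs more and the effect interval excludes zero on the side of readmissions avoided. Otherwise state which arm dominates, or that the ratio is undefined.

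This takes a few sentences and no new data; the bootstrap standard errors and correlation supply every input. The downside is that the main summary becomes a curve over thresholds instead of a single figure.
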